### 2.3. Study purpose

To evaluate the differential expression of miRNAs in patients with CAPS and healthy controls, to provide new biomarkers for diagnosis of CAPS.To explore the association between the changes of miRNAs and the efficacy of duloxetine treatment at week 4, 12, 24 and 36 in patients with CAPS.

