#### 2.11.3. Laboratory measurements.

In Clinical Laboratory of Shanghai Ruijin Hospital, blood routine and biochemical indicators will be tested. In laboratory of Gastroenterology, based on the experimental method of Real-Time Fluorescence Quantitative PCR, the miRNA will be sequenced.

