### 2.12. Statistical analysis

#### 2.12.1. Sample size calculation.

Taking the bilateral test α = 0.05 and 1-β (power of test) = 0.95, the total sample size of the patients group is 172 cases. According to the 20% shedding or elimination possibility, the sample size of patients group is 215 cases. According to the allocation 1:1, the healthy control group is 215 cases.

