#### 2.12.2. Data analysis.

Statistical Package for the Social Sciences for Mac book air, version 26 will be used for data analysis. For descriptive statistics, we use proportions for categorical variables, mean ± SD for normal continuous data, median for non-normally continuous data. K-S tests will be used for the normality test. Descriptive statistic is used to describe the demographic characteristics and laboratory test results. Whole data of primary and secondary outcomes are repeated measure and continuous data. X2 test is used for comparison at different time points and intergroup differences in term of baseline data. If the difference is detected statistically significant, post hoc multiple pairwise comparison will be performed. The association of blood biomarkers, plasma concentration, genotype and clinical efficacy, medication adherence will be assessed by Spearman correlation analysis. *P* < 0.05 is considered statistically significant.

We use intention to treat and per protocol to deal with missing values, outlier values, lost follow-up and non-adherence respectively.

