## 3. Discussion

CAPS is characterized by chronic pain, which is a major cause of disability in the world.^[12]^ However, accurate diagnosis and treatment of CAPS are still difficult. Therefore, it is warranted to explore the specific biomarkers for CAPS to help the diagnosis and treatment. miRNAs regulate gene expression, significantly extracellular miRNAs are abnormally expressed in serum during the process of disorders.^[13]^ Although studies on miRNA relationship with CAPS were insufficient, the studies on IBS which is another functional gastrointestinal disorders characterized by recurrent abdominal pain, are more in-depth. It has already been show that miR-29 family (29a 29b 29c)was significantly correlated with pathogenesis of IBS by modifying intestinal permeability in IBS patients,^[14]^ furthermore, miRNA-29a reduced HTR7 expression, which due to hypersensitivity in IBS because HTR7 weaken visceral hyperalgesia.^[15]^ Interestingly, in our pilot study, we also found 7 miRNAs, namely hsa-miR-415a, hsa-miR-26a-5p, hsa-miR-181a-5p, hsa-miR16-5p, hsa-let-7g-5p, hsa-miR-25-3p, hsa-miR-423-3p were up-regulated and 4 miRNAs, namely hsa-miR-126-3P, hsa-miR-23a-3p, hsa-let-7b-5p, hsa-let-7i-5p were downregulated in CAPS groups compared with healthy control groups (Fig. 3). Therefore, we can presume that the expression of particular miRNA may become a potential diagnostic biomarkers in the future.

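### One P < 0.05 threshold covers an unspecified number of miRNAs, two primary outcomes and four post-baseline visits, with no adjustment named

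*Protocol article*

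**What the plan says.** All references are to the protocol article.

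- **Decision rule.** Section 2.12.2 (Data analysis) gives one threshold for P: "0.05 is considered statistically significant". It names no family-wise or false-discovery-rate method and no order of testing. Pairwise comparisons follow only if an overall difference is significant. Associations of biomarkers, plasma concentration, genotype, efficacy and adherence are assessed by Spearman correlation.
- **Sample size.** Section 2.12.1: "Taking the bilateral test α = 0.05" and "1-β (power of test) = 0.95", from which "the total sample size of the patients group is 172 cases". Alpha is not divided.
- **Primary outcomes.** Section 2.10.1 has two: the baseline difference in miRNA expression between patients and controls, and the change in pain score together with its relation to miRNA change. Neither names the miRNAs, and the second names no primary visit.
- **Visits.** Section 2.3 sets out to study "the association between the changes of miRNAs and the efficacy of duloxetine treatment at week 4, 12, 24 and 36".
- **Panel.** Section 2.11.3 says "based on the experimental method of Real-Time Fluorescence Quantitative PCR, the miRNA will be sequenced", without a list. The Discussion reports pilot candidates ("in our pilot study, we also found 7 miRNAs" that were up-regulated, plus four that were down-regulated), but nothing restricts testing to these 11.

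**The concern.** Each primary outcome is a family of tests of unknown size. If every miRNA, at every visit, may be called significant at 0.05, the probability that at least one null miRNA is declared a biomarker exceeds 5% and grows with the panel. Leaving the panel and the primary visit open also allows them to be chosen after the results are seen.

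The abstract and the Discussion say the findings will give a reliable basis for diagnosing CAPS and for predicting duloxetine efficacy. A diagnostic or predictive miRNA reported under this rule could be a chance result, and readers would not know how many tests lay behind it.

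**Working it through.** **The plan's own figure.** Section 2.12.1 adds 20% for losses: 172 / (1 − 0.20) = 215, which agrees with the text. The 172 itself cannot be reproduced, because no effect size, standard deviation or test is given. The article states no family-wise error rate to check.

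**Inputs**

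- Per-test level 0.05 (section 2.12.2).
- Panel of m miRNAs: not stated. I assume the 11 pilot miRNAs (7 + 4, Discussion).
- Four post-baseline visits (section 2.3).
- Every null hypothesis is taken as true.

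**Formulas.** For k independent tests, P(at least one false positive) = 1 − 0.95^k, and the expected number of false positives is 0.05k. For correlated tests, the statistics were simulated with a common pairwise correlation rho (20,000 runs).

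**Number of tests**

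- Baseline comparison: k = 11.
- Association with pain change: k = 11 × 4 = 44.
- Both primary outcomes: k = 11 + 44 = 55.

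| k | Independent | rho 0.3 | rho 0.5 | rho 0.8 | Expected false positives |
|---|---|---|---|---|---|
| 11 | 1 − 0.95^11 = 43% | 37% | 30% | 18% | 0.55 |
| 44 | 1 − 0.95^44 = 90% | 77% | 60% | 29% | 2.2 |
| 55 | 1 − 0.95^55 = 94% | 83% | 64% | 31% | 2.75 |

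Correlation lowers the chance of any false positive but not the expected number. A larger baseline panel raises the chance: with independent tests, 50 miRNAs give 1 − 0.95^50 = 92% and 100 give 1 − 0.95^100 = 99.4%.

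**Effect of adjustment on power.** This needs an assumed effect. If 172 per group came from comparing two means at two-sided 0.05 with 95% power, the implied standardised difference is d = (1.960 + 1.645) × √(2/172) = 0.389. Bonferroni over 11 gives 0.05/11 = 0.0045, critical value 2.838.

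- With 172 per group: d × √(172/2) = 3.605, and power is Φ(3.605 − 2.838) = 78%.
- With all 215 per group measured at baseline: d × √(215/2) = 4.030, and power is Φ(4.030 − 2.838) = 88%.
- Restoring 95%: n = 2 × (2.838 + 1.645)² / 0.389², about 266 evaluable per group.

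**The case against.** **Only an article is shown.** A full protocol or analysis plan may hold the miRNA list and a correction. Adjusted P values can also be read against 0.05, so the sentence does not rule out adjustment. Both points are fair. But the article does more than stay silent: it states a single threshold, sizes the study at an undivided alpha, and spreads the primary outcomes over an open set of miRNAs and four visits. Followed as written, this inflates the error rate.

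**There is a gate.** Pairwise comparisons depend on a significant overall result, so it would be wrong to say that every visit contrast is tested freely. The gate still does not act across miRNAs or scales, and it does not cover the correlations.

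**A reader might infer that false biomarkers are close to certain.** The documents do not support that in general. With the 11 pilot miRNAs the baseline figure is 43% or less. Figures near 100% need a broad panel, or a full grid such as 11 miRNAs × 4 visits × 7 scales = 308 tests (15.4 expected false positives). The article does not specify that grid, and 11 × 4 × 6 = 264 of its tests concern secondary scales, which do not affect the primary error rate. Every figure also takes all nulls as true. For miRNAs selected because they differed in the pilot, that is the extreme case at baseline.

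**A reader might infer that the panel could be a sequencing screen.** Sections 2.7 and 2.11.3 both name quantitative PCR as the method, so the loose verb is weak evidence of that. What stands is that the number of miRNAs is not given.

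**The aim is exploratory.** Section 2.3 partly says so, but these outcomes are labelled primary and the promised conclusions are firm ones.

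**Conclusion.** The concern holds in this form: a flat 0.05 threshold, with no adjustment named, governs an unspecified number of miRNAs, two primary outcomes and four visits. The chance of at least one false primary finding lies well above 5% in every case computed, from 18% (11 baseline tests, rho 0.8) to 94% (55 independent tests). These figures rest on an assumed panel of 11, a common correlation between tests, and all nulls being true. True signals would lower them and a larger panel would raise them. The article does not support a claim that false positives are inevitable, or that multiplicity is ignored at every step.

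**What to change.** Replace the flat rule in section 2.12.2 before any data are examined:

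1. Fix the miRNA list for each question. The 11 pilot miRNAs were chosen for differences between patients and controls. Nothing in the article supports them as the only family for duloxetine response: of the duloxetine-related miRNAs cited in the Introduction and Discussion, only miR-16-5p is among them.
2. Baseline: apply Benjamini-Hochberg at 5%, or Holm, over all miRNAs tested.
3. Association with change in the pain score (NRS): apply the same control over all miRNA-by-visit tests, or over miRNAs at one primary visit named in advance.
4. Either split the 5% between the two primary outcomes or state that each is controlled separately. Separate family-wise control at 5% allows up to 1 − 0.95² = 9.75% overall if the two are independent.
5. Label associations with secondary scales, genotype, plasma concentration and adherence as exploratory.
6. Restate the 95% power in section 2.12.1 for the adjusted threshold.

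The cost is mostly wording, fewer nominally significant results and some power. At the assumed d = 0.389 with 172 per group, Bonferroni over 11 takes per-miRNA power from 95% to about 78%. False-discovery-rate control would usually lose less.

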### 2.8. Criteria for discontinuing the intervention

Sever adverse reactions; Any other disease which affects the efficacy of duloxetine, and determination of Adverse events; Patient is deemed unsuitable for continuing to take duloxetine by the researchers; Subjects withdraw informed consent form; Patients are reluctant to continue their treatment because of poor efficacy; and Lost to follow up.

The reasons for discontinuation and withdrawal would be recorded on the case report form. Subjects who signed informed consent but did not accept the intervention will be replaced. Subjects who signed informed consent, accept the intervention and subsequently withdraw will or may be not replaced.

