### 2.9. Lost to follow-up

Participant stops scheduled study follow-up; participant fails to complete study-prescribed procedures; and loss the connection with participant.

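### Intention to treat and per protocol are named as the handling of missing and outlying scores, which they are not; selective dropout can then overstate the before-after pain improvement

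*Protocol article*

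**What the plan says.** All places are in the protocol article.

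- **Section 2.12.2 (Data analysis):** "We use intention to treat and per protocol to deal with missing values, outlier values, lost follow-up and non-adherence respectively". The same section describes the outcomes as repeated and continuous. The analyses it names are a chi-square test, post hoc pairwise comparisons and Spearman correlation.
- **Section 2.8 (Criteria for discontinuing the intervention):** the listed reasons include severe adverse reactions, loss to follow-up, and "Patients are reluctant to continue their treatment because of poor efficacy". On replacement, it says: "Subjects who signed informed consent, accept the intervention and subsequently withdraw will or may be not replaced".
- **Section 2.9 (Lost to follow-up):** one of the three listed items is "participant fails to complete study-prescribed procedures".
- **Section 2.12.1 (Sample size calculation):** "According to the 20% shedding or elimination possibility, the sample size of patients group is 215 cases". The figure before inflation is 172.
- **Section 2.10.1 (Primary outcome):** there are two primary outcomes. One is the baseline miRNA comparison between patients and controls. The other is the change in abdominal pain score on duloxetine in the patient group, with its relation to the change in miRNA.

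**The concern.** Intention to treat and per protocol are analysis sets: they settle who is counted and how non-adherence is treated. A patient in the intention-to-treat set with no pain score at a visit still has no score, and an outlying value is equally untouched by the choice of set. The pairing also fails, because two sets are matched item by item to four problems. On the kindest reading, per protocol goes with non-adherence and intention to treat with the other three. Missing values and outliers are then still assigned to something that does not handle them.

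This matters for the pain outcome. It is a before-after change in one treated group, so no randomised comparator offsets selective loss. If patients who do badly are more likely to lack later scores, or are removed from a per-protocol set, the remaining average looks better than the average in everyone treated.

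**Working it through.** **1. The plan's own loss figure.** 172 / (1 − 0.20) = 215, which matches Section 2.12.1. The plan therefore allows for up to 215 − 172 = 43 patients without usable data.

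**2. Do the named analyses use incomplete patients?** A before-after pairwise comparison needs both scores. A correlation of changes needs both scores and both miRNA values. A chi-square comparison of time points counts only those observed at each one. With nothing else named, a missing score drops out of the comparison that needs it, and the intention-to-treat analysis becomes an observed-case analysis.

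**3. Size for the mean pain change.** Let *d* be the fraction lost, C the mean improvement in completers and L the mean improvement in those lost.

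- Mean in all treated patients = (1 − d) × C + d × L
- Overstatement in points = d × (C − L)

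Here d = 0.20 comes from Section 2.12.1. C = 2.5 and the values of L are assumptions, because the article gives no expected change.

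| Those lost (20%) | L | Mean in all treated | Overstatement |
|---|---|---|---|
| Same as completers | 2.5 | 0.8 × 2.5 + 0.2 × 2.5 = 2.50 | 0 points, 0% |
| Half as completers, half no improvement | 1.25 | 2.0 + 0.2 × 1.25 = 2.25 | 0.25 points, 11% |
| All improve by 1 point | 1.0 | 2.0 + 0.2 × 1.0 = 2.20 | 0.30 points, 14% |
| None improve | 0 | 2.0 + 0 = 2.00 | 0.50 points, 25% |

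**4. Cross-check on the response scale.** The Introduction cites 71% effectiveness of duloxetine in CAPS; it is used here only as an illustrative true rate R. Let *s* be the share of those lost who are non-responders leaving for poor efficacy, the rest being lost at random.

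- Observed rate = (R − d × (1 − s) × R) / (1 − d)
- s = 0: (0.71 − 0.142) / 0.8 = 71.0%
- s = 0.5: (0.71 − 0.071) / 0.8 = 79.9%
- s = 1: 0.71 / 0.8 = 88.75%

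The bias runs from 0 to about +17.8 percentage points. The documents do not give *s*.

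**5. The pain-miRNA association.** Losing the poorest responders narrows the spread of pain change, which tends to weaken a correlation. In simulated bivariate normal data with the worst 20% on the outcome removed (an assumed, extreme selection), Spearman's coefficient fell from 0.29 to 0.22 and from 0.48 to 0.39. Other dropout patterns could act differently.

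**6. The baseline miRNA comparison.** It uses only first-visit samples, so dropout after baseline does not touch it.

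**The case against.** The strongest reply is that a journal article condenses a fuller plan, which may name a proper model. That holds for an omission: the absence of an imputation method or a named model would not be a finding by itself. It does not cover a method that is stated and cannot do what is claimed, and a fuller plan written to follow this sentence would inherit the fault.

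Other parts of the reply stand, and they limit the point.

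- **A reader might infer that the pain result will be biased.** The article does not say so. It states no complete-case rule and does not make week 24 the single analysis time. The study timeline (Table 1) records the pain score at all five visits. Section 2.8 concerns stopping the drug and does not say that scores stop being collected. Informative loss is plausible from the listed reasons but is not written into the plan.
- **A reader might infer that the miRNA association would be overstated too.** Nothing in the documents supports that, and step 5 points the other way under one simple pattern.
- **A reader might take 14% to 25% as the size.** That range assumes every lost patient is a poor responder. The plan's 20% also covers eliminations, which may have nothing to do with efficacy, so an honest range starts at 0%.
- **A reader might take Section 2.9 to class a patient as lost after one missed blood draw.** Its three items are joined by a conjunction and may be meant jointly. The text is ambiguous, not shown to be wrong.
- **A reader might take Section 2.8 to allow replacement of treated dropouts, enriching the sample with patients who do well.** The preceding sentence says that untreated consenters are replaced, and the contrast suggests that treated withdrawals are not. The phrase "accept the intervention and subsequently withdraw will or may be not replaced" is unclear, and enrichment is speculation.

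**Conclusion.** The concern holds in a limited form. The sentence in Section 2.12.2 is wrong as a statement of method: two analysis sets are given the job of handling missing and outlying scores, and nothing else in the article does that job. With poor efficacy and severe adverse reactions among the reasons for stopping, 20% loss planned and a single treated group, an observed-case or per-protocol before-after analysis can overstate the mean pain improvement. The size is 0% if loss is unrelated to efficacy and up to about 25% if completers improve by 2.5 points and all those lost by none. Those changes are assumed. The actual figure also depends on how many patients leave for poor efficacy, whether scores are collected after stopping, and what any fuller plan adds.

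One of the two primary outcomes is intact, and the sample size of 215 stands. This should be fixed, but it does not undermine the study as a whole.

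**What to change.** 1. **Separate the two ideas in Section 2.12.2.** Define the main set as all patients who took at least one dose, with per protocol as supportive only. State the handling of missing and outlying values on its own.
2. **Name a model for the pain score.** Use a likelihood-based repeated-measures model with every observed visit, and state its missing-at-random assumption.
3. **Add one sensitivity analysis.** Set patients who stop for poor efficacy or an adverse reaction to no improvement, or use a delta-adjusted imputation.
4. **Keep outliers** in the main analysis, with a rank-based check.
5. **Keep collecting the scheduled pain scores after the drug is stopped.** This is the most urgent item, since scores not collected cannot be recovered later.
6. **Clarify two definitions.** State in Section 2.8 that treated withdrawals are not replaced, since the 20% inflation already covers them. State in Section 2.9 that a single missed procedure does not make a patient lost to follow-up.

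The cost is minor analysis work and rewording, a few extra questionnaires from patients off the drug, and possibly a less favourable estimate. The sample size does not change.

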## 3. Discussion

CAPS is characterized by chronic pain, which is a major cause of disability in the world.^[12]^ However, accurate diagnosis and treatment of CAPS are still difficult. Therefore, it is warranted to explore the specific biomarkers for CAPS to help the diagnosis and treatment. miRNAs regulate gene expression, significantly extracellular miRNAs are abnormally expressed in serum during the process of disorders.^[13]^ Although studies on miRNA relationship with CAPS were insufficient, the studies on IBS which is another functional gastrointestinal disorders characterized by recurrent abdominal pain, are more in-depth. It has already been show that miR-29 family (29a 29b 29c)was significantly correlated with pathogenesis of IBS by modifying intestinal permeability in IBS patients,^[14]^ furthermore, miRNA-29a reduced HTR7 expression, which due to hypersensitivity in IBS because HTR7 weaken visceral hyperalgesia.^[15]^ Interestingly, in our pilot study, we also found 7 miRNAs, namely hsa-miR-415a, hsa-miR-26a-5p, hsa-miR-181a-5p, hsa-miR16-5p, hsa-let-7g-5p, hsa-miR-25-3p, hsa-miR-423-3p were up-regulated and 4 miRNAs, namely hsa-miR-126-3P, hsa-miR-23a-3p, hsa-let-7b-5p, hsa-let-7i-5p were downregulated in CAPS groups compared with healthy control groups (Fig. 3). Therefore, we can presume that the expression of particular miRNA may become a potential diagnostic biomarkers in the future.

**Figure 3. F3:**
[figure not shown]
Pilot study result. hsa-miR-415a, hsa-miR-26a-5p, hsa-miR-181a-5p, hsa-miR16-5p, hsa-let-7g-5p, hsa-miR-25-3p, hsa-miR-423-3p were up-regulated and hsa-miR-126-3P, hsa-miR-23a-3p, hsa-let-7b-5p, hsa-let-7i-5p were down-regulated in CAPS group compared with healthy control group. CAPS = centrally mediated abdominal pain syndrome.

Duloxetine has pain modulating effects which beyond its psychiatric indications, which has been used widely for the functional gastrointestinal disorders.^[16]^ Juan Pablo Lopez et al found that differential expression of miR-146a- 5p, miR-146b-5p, miR-425-3p and miR-24-3p after dolextine treatment for patients with depression in a large, randomized placebo-controlled trial.^[17]^ Accordingly, we believe that miRNA may emerge as a potential predictor of efficacy of duloxetine treatment for patients with CAPS.

Our study has some advantages. Firstly, our study is a prospective study on CAPS. Secondly, our study provides a comprehensive assessment of clinical characteristics, psychological status, quality of life, sleep quality and biomarkers for CAPS. It is worth mentioning that this study may be the first perspective cohort study to explore miRNAs in serum as a diagnostic biomarker and a predictor of efficacy of duloxetine treatment for CAPS.

In a word, this study is helpful to provide the reliable basis for diagnosis and the predictor of duloxetine efficacy of CAPS. Our results will shed significant new light on the development of CAPS.
